#### Executive Functions Battery

Inhibitory/interference control: (1) Flanker and (2) Go/No-GoWorking memory/updating: (3) N-Back and (4) Running SpanCognitive flexibility/switching: (5) Attention Switching Task (AST) and (6) Dots/Triangles

Stimulus acquisition and presentation in all 6 tasks are controlled by Presentation software. Response button boxes (Cedrus RB-844), connected to 30 identical Hewlett-Packard laptops, registered responses very accurately.

##### Flanker Task

The current task battery makes use of an adapted version of the original Eriksen Flanker task [24] to measure children’s response interference control abilities. In this adapted version, letters are used instead of arrows to avoid the well-documented developmental ceiling effects associated with the traditional arrow flanker task, which is found at around 10 years of age in normally developing children [25].

 An array of 3 letters is presented at the center of the screen. The middle letter is the target letter and the other 2 are flankers. Participants are instructed to press the left button on the Cedrus RB-844 response button box when the target letter is a B or H, and the right button if the target is letter F or T—while ignoring the flanking stimuli (two B’s, H’s, F’s, or T’s).

Textbox 1. Overview of the outcome measures.
**Primary Outcomes**
Executive functions: Computer task batteryWorking memory: N-Back; Running SpanImpulse control: Flanker; Go/No-GoCognitive flexibility: Attention switching task; Dots/triangles
**Secondary Outcomes**
Emotion-regulation, attention, healthy behaviors: SurveyEmotion-regulation: FEEL-KJ (Fragebogen zur Ehrebung der Emotionsregulation bei Kindern und Jugendlichen; Questionnaire for the Assessment of Emotion Regulation among Children and Adolescents)Mental health—social/emotional/behavioral functioning: Strengths and Difficulties QuestionnaireAttention-Related Cognitive Errors (Scale; ARCES)Physical Activity Questionnaire (PAQ-C)Dietary habitsDeterminants of dietary habits and physical activityDemographicsAdditional data from provincial database: socioeconomic status and academic performance (CITO; Centraal Instituur voor Toetsontwikkeling; Central Institute for the Development of Tests; a standardized test of academic performance, widely used in the Netherlands)

There are 3 stimulus conditions:

Stimulus-response congruent (C) condition: no response conflict (eg, B B B)Stimulus incongruent (SI) condition: target and flankers are different letters but both are mapped to a response of the same hand so that there is stimulus conflict but no response conflict (B H B; H B H; F T F; T F T)Stimulus and response incongruent (SRI) condition in which the flankers and target differ in both the physical appearance (stimulus conflict) and the required response hand (response conflict; eg, F B F; H T H).

A total number of 144 trials are presented in 3 blocks of 48 trials. Each of the 3 conditions is randomly presented with equal probability within task blocks. Each trial starts with the presentation of 2 flanking stimuli for 200 ms (to establish flanker priming effects), after which the middle target letter appears and the entire array of 3 letters stays on the screen for 700 ms, followed by a fixed interstimulus interval (ISI) of 500 ms, during which a fixation cross is presented. The maximum response window is 1400 ms. The experimental task (no feedback) is preceded by a practice block of 18 trials in which the feedback: “correct,” “wrong,” or “faster” is given. To measure the executive function *response interference control* the accuracy and reaction time of participants in the C and SRI conditions will be compared.

##### Go/No-Go

In the current Go/No-Go task, the participants are presented with a random series of letters drawn from the alphabet and appearing one by one in the center of the computer screen. The participants’ task is to respond to every letter by pressing the right button on a Cedrus RB-844 response box (Go stimuli), but to refrain from responding when they see the letter X (the No-Go stimulus). Each trial lasts 1200 ms, with a stimulus presentation rate of 500 ms and a fixed ISI of 700 ms. A total of 200 trials are presented in 2 blocks of 100, with a pause in between. Within each task, the probability that a No-Go stimulus will appear is 10.0% (main task: twice 10/100). The experimental task (no feedback) is preceded by a text instruction screen and 15 practice trials (feedback is only given when a participant incorrectly responds to the No-Go stimulus). The Go/No-Go task has been widely used to study the development of response inhibition [26].

##### N-Back

This version of the N-back task has been used to investigate the development of nonspatial working memory capacity among children and adolescents [27]. Semirandom sequences of letters (A, B, F, G, H, K, L, S, T, W, X, Z) appear one at a time in the center of the screen. Letters (height: 1 cm, width: 0.5 cm) are black and presented between 2 black vertical bars (height: 1.5 cm) on a gray background. The current N-back task consists of 1- and 2-back conditions. Participants are instructed to respond by pressing a Cedrus button box RB-844, with their right index finger, whenever they detect a target event. In 1- and 2-back conditions a target is, respectively, defined as a letter that is identical to the letter presented 1 (eg, T-T), or 2 trials back in the sequence (eg, A-B-A). The experimental task consists of a total of 200 trials, presented in 4 blocks of 50 stimuli, 2 blocks per condition. The order of the block presentation is: 1-back – 2-back – 1-back – 2-back. All blocks have an identical target frequency of 36% (18/50). Each trial lasts 2000 milliseconds (ms) with a stimulus duration of 500 ms and a fixed ISI of 1500 ms. The experimental tasks are preceded by several instruction screens with pictures explaining the specific task requirements, directly followed by 20 practice trials (target event frequency 40%, 8/20) during which feedback is given (“wrong” for false alarms and “missed” when a target-event is not detected). Due to the complexity of the 2-back blocks, a second practice session of 20 trials is automatically run when the success rate in the first practice block falls below 70% (14/20). No feedback is given during the experimental/real tasks.

##### Running Span Task

In this task, a series of numbers varying in length are presented one by one at the center of the computer screen. Each number series is preceded by “The next rows of numbers will follow. If you are ready, press ENTER,” after which the series starts. Within a series, each digit is presented for 1 s with an interval of 500 ms between them. Following the presentation of the entire sequence, participants are presented with a screen showing the presented sequence with the last 3 numbers displayed as 3 question marks. The participants have to recall these 3 missing numbers from working memory and type them in the spaces indicated by the question marks by using the number buttons on the laptop keyboard and ENTER when finished. For example: if series 4, 2, 5, 8, 3, and 9 is presented, the participant sees “4 2 5 ? ? ?” on the screen and has to enter 8, 3, 9 in the spaces represented by the question marks.

In the present task, 12 number series are presented that differ in length; there are 4 series each of 5, 6, and 7 digits that are presented randomly so that participants cannot predict series length. In each case, the last 3 digits of a series have to be recalled. The experimental part of the task—during which no feedback is given—is preceded by instruction screens explaining the task followed by 2 practice trials with feedback. The dependent measures in this task are the mean percentage of correctly completed trials per series length and the average time at which the enter button is pressed once the missing numbers are entered. A similar version of this running span, the digit memory task, has been used before to measure updating in children [28].

##### Attention Switching Task (AST)

The present task is an adapted version of the task previously used in 2 developmental studies by Cepeda et al [29,30]. The task consists of 3 blocks: 2 nonswitch blocks (2 x 32 trials) precede 1 switch block (64 trials). On each trial, 1 of the 4 possible stimulus displays is presented (1, 111, 3, or 333). In the first block, the instruction “which number?” precedes the stimulus 1 or 111 and is correctly responded to by pressing the left button on the Cedrus RB-844 button box (and right button for 3 or 333). In the second block (“how many numbers?”), the left response button represents the single digits (1 and 3), whereas the right button is associated with a string of 3 digits (111 or 333), irrespective of the identity of the digits. In the third block (the switch block), cue instructions (“which number?” or “how many numbers?”) alternate randomly, meaning that participants have to switch between instructions on about half of the trials. Every trial starts with the presentation of the cue, followed by the stimulus after 200 ms. Both remain on the screen until a response is given. Each experimental block commences with instruction screens explaining the task and allowing the participants to practice each stimulus-response configuration. Feedback is given during the entire task (“wrong” or “faster,” no feedback for correct responses).

##### Dots/Triangles

This task is adapted from the original [22] in several ways: (i) Diagram instruction screens have been inserted, (ii) feedback is given after every trial during the practice period (for 1000 ms) rather than after the entire block, (iii) no feedback is given during the experimental blocks, (iv) a minimum for the difference between the amounts of dots and triangles is set at 2, (v) the entire task has been shortened, (vi) in the third and last block, rules switch every 3 trials (instead of every 4 trials). Blocks 1 and 2 are nonswitch and consist of 30 trials (preceded by 5 practice trials). The third block (switch) consists of 93 trials (63 non-switch and 30 switch) and is preceded by 15 practice trials. Every trial starts with a blank screen for 1000 ms, followed by an empty 4 x 4 grid presented for 1000 ms, after which the dots or triangles appear and remain visible until a response is given. Feedback is only given during practice trials (“correct,” “wrong,” and “too fast”), and appears for 500 ms directly after a response is given, before the next empty grid is presented. The ISI duration in practice and experimental trials is the same, as feedback is given during the ISI interval (500 ms). A previous study with 7- and 11-year-old children identified a relatively early maturation mechanism associated with task-set inertia and a later maturing mechanism relating to task-set reconfiguration [31]. Figure 1 shows how the testing laptops and response button boxes are best setup at the elementary school.

### Questionnaires

#### Children

In addition to EFs, we were also interested in more behavioral outcomes, for which we compiled a Web-based questionnaire (pilot-tested: 1 hour to complete) comprising:

##### Feel-KJ

This questionnaire measures 15 (mal)adaptive emotion regulation strategies in relation to anxiety, sadness, and anger: (1) Problem Solving (eg, “I try to change what makes me angry”), (2) Distraction (eg, *when I am sad…* “I do something fun”), (3) Forgetting (eg, “I try to forget what makes me angry”), (4) Acceptance (eg, “I make the best of it”), (5) Humor Enhancement (eg, I think about things that make me happy”), (6) Cognitive Problem Solving (eg, I think about how I can solve the problem”), (7) Reevaluation (eg, “I tell myself it is nothing important”), (8) Giving Up (eg, “I don’t want to do anything”), (9) Withdrawal (eg, “I don’t want to see anyone”), (10) Rumination (eg, “I cannot get it out of my head”), (11) Self-Devaluation (eg, “I blame myself”), (12) Aggressive Actions (eg, “I get into a quarrel with others”), (13) Social Support (eg, “I tell someone how I am doing”), (14) Expression (eg, “I express my sadness”), and (15) Emotional Control (eg, “I keep my feelings to myself”). There is a total of 90 items (2 items x 15 strategies x 3 emotions). In a previous research, exploratory factor analysis has suggested that the first 7 (1-7) strategies can be classified as Adaptive Emotion Regulation, the next 6 ( 8-13) as Maladaptive, and that the remaining Social Support, Expression, and Emotional Control strategies could not be classified as Adaptive or Maladaptive Emotion Regulation [32].

**Figure 1 figure1:**
[figure not shown]
Example of an executive function (EF) testing station setup at an elementary school.

Internal consistency has repeatedly been found to be high, also among children [33]. We included the Dutch version [33] of the FEEL-KJ to be used in our outcome measurement.

##### Strengths and Difficulties Questionnaire (SDQ)

The SDQ is a behavioral screening questionnaire that assesses 3 domains of children’s overall mental health: social, emotional, and behavioral functioning [34]. A total of 25 items are evenly distributed among 5 scales: (1) Conduct Problems (eg, lying and stealing: “I am often accused of lying or cheating”), (2) Inattention Hyperactivity (eg, impulsivity and concentration problems: “I am easily distracted”), (3) Emotional Problems (eg, unhappy mood and worries: I am often unhappy, down-hearted or tearful), (4) Peer Problems (eg, being bullied: “Other children or young people pick on me or bully me”), and (5) Prosocial Behavior (eg, sharing and being helpful: “I am helpful when someone is hurt, upset or feeling ill”). Items are rated on a 3-point Likert Scale, with 0 representing “not true,” 1 representing “somewhat true,” and 2 representing “certainly true.” Several items are reverse-scored. The first 4 subscales summed up together give a total difficulty score ranging from 0 to 40, with a higher score indicating more difficulties. The Prosocial Behavior subscale reflects the strengths of the individual. The SDQ is an internationally approved instrument of value due to its brevity and psychometric properties [35]. In terms of internal consistency, one study among 7- to 15-year-old Finnish children and adolescents reported a Cronbach alpha of .71 [36]. We included the Dutch version of the SDQ [37] to be used in our outcome measurement.

##### Attention-Related Cognitive Errors Scale (ARCES)

The ARCES consists of 12 questions measuring everyday mistakes as a result of not paying sufficient attention to the task at hand, also called mind-wandering [38]. Example questions include: “I make mistakes because I am doing one thing and thinking about another” and “I fail to see what I am looking for even though I am looking right at it.” The 12 items are rated on a 5-point Likert Scale ranging from 1 representing “never” to 5 representing “very often.” A mean score is computed for each individual by summing the scores of all questions. The ARCES has been rigorously validated and normed [38]. We included a back-translated Dutch version of the ARCES, with some questions adapted to make them suitable for children, to be used in our outcome measurement.

##### Physical Activity Questionnaire-Child (PAQ-C)

The PAQ-C is an instrument used to assess self-reported levels of physical activity during the past 7 days for 8- to 14-years-old students [39]. The PAQ-C provides a summary physical activity score derived from 9 items, each scored on a 5-point scale. Examples include: “In the last 7 days, during your physical education (PE) classes, how often were you very active (playing hard, running, jumping, throwing)? Response options (check one only) are: “I don’t do PE,” “hardly ever,” “sometimes,” “quite often,” “always.” Or, “In the last 7 days, how many evenings did you do sports, dance, or play games in a very active way?” Response options are (check one only) “none,” “1 time last week,” “2 or 3 times last week,” “4 or 5 times last week,” “6 or 7 times last week.” The scale concludes with a small agenda (7 week days) on which the child marks how often he or she did physical activity for each day last week (“none” to “very often”). Excellent content validity, acceptable interitem reliability and a moderate to good strength of interrater agreement has been found for the Dutch PAQ-C [40].

##### Dietary Habits

The same eating behaviors as were addressed in the eHealth module of this study (consumption of vegetables, fruit, sugary beverages, and unhealthy snacks) are briefly assessed using 2 items per behavior taken from an existing questionnaire [41]. For example: “How many days in the past week did you eat fruit?” and “How many pieces of fruit on average did you eat per day?”

##### Determinants of Dietary Habits and Physical Activity

Attitude, Social Influences, and Self-Efficacy are measured for the 5 behaviors targeted in the eHealth module (physical activity, consumption of vegetables, fruit, sugary beverages, and unhealthy snacks). For example: Attitude: “Eating 3-4 serving spoons of vegetables a day would be (1 “very unpleasant” – 7 “very pleasant”) for me”; Self-Efficacy: “I am confident I would be able to eat at least 2 pieces of fruit each day, if I wanted to” 1 “very untrue” – 7 “very true” [20].

#### Demographics

The questionnaire package started with a short demographic background (age, school, country of birth child and parents, gender, dominant hand [as a control variable for the EF battery response button box]). Further demographic details were collected from the parents (Socioeconomic Status—a correlate of EF [42], medication).

To ensure maximal participation, both the EF test battery and the Web-based questionnaire were administered at school. Moreover, 30 identical laptops and response button boxes were used to ensure maximum accuracy in measuring reaction times. Administration of the task battery and questionnaires took place on different days, to minimize load and maximize children’s motivation to keep performing well. Everyone was measured within a span of 5 weeks, right before the start of the intervention and immediately after it ended. Trained research assistants (graduated psychology masters) were present at all times to supervise and instruct in the classrooms, as well as help slow readers work their way through the survey, when needed (this only happened a few times). All questionnaires had been normed for our age group, indicating readability should be decent. The task battery was administered in small groups of 5, the questionnaire in the entire group at once. While completing the computer task battery in small groups, children wore special noise-canceling headphones to avoid distraction. Furthermore, scores below chance levels (which indicates random responses) will be removed from the dataset. The strain on children was not small by any standards, but satisfactory pilot-testing and similar experiences in the field by supervising professors on the project team gave us confidence that the setup of measuring would run smoothly—which it did. The measurements concluded with a brief assessment of weight and height (body mass index, BMI). These anthropometrics were measured using standard procedures [43]. Both height (using the SECA 213 stadiometer) and weight (using the SECA 877 scales) were assessed without shoes or heavy clothing to the nearest 1 mm and 0.1 kg, respectively. BMI was calculated as weight/height squared (kg/m^2^) and Z-scores from age- and sex-specific reference values. Academic performance will also be taken into account during analysis using standardized national test scores (ie, CITO, the most widely used test in the Netherlands, designed by Centraal Instituur voor Toetsontwikkeling).

#### Teachers

Teachers are a valuable source of information regarding the children but were not included in the measurements because their time is very limited and scoring an entire class group is time-consuming. However, during the program implementation, close contact between teachers and the development team was maintained, to gain insight in the workings and feasibility of the intervention materials. Continuous feedback was encouraged and welcomed, to further improve and fine-tune the games and activities. After the intervention had taken place, an extensive (process) evaluation followed, including an assessment of fidelity and completeness.

#### Parents

We did include parents, for whom we composed a Web-based questionnaire pertaining questions about their child’s behavior. This was mainly because self-report questionnaires given to 9- to 11-year-old children could not provide an accurate overview. Note: we will only describe the BRIEF-parent scale in the following overview, as the rest of the measurements are similar to those administered directly to the children, but then from the parent *about* their child.

The Web-based questionnaire for parents included:

Strengths and Difficulties QuestionnaireBehavior Rating Inventory of Executive Function (BRIEF-parent). The BRIEF is an 86-item rating scale developed to assess, via parent and teacher reports, manifestations of executive function in the everyday lives of children aged 5-18 years [44]. The BRIEF yields an overall Global Executive Composite score composed of 2 indexes called the Behavioral Regulation Index (child’s ability to Inhibit [impulses], Shift [between tasks], and Emotional Control) and the Metacognition Index (child’s ability to Initiate [start a task], Working Memory, Plan/Organize, Monitor [their own behavior], and Organization of Materials)Attention-Related Cognitive Errors Scale (ARCES)Child’s physical activity and dietary habitsDemographics (including socioeconomic status)

### Statistical Analyses

As it was not feasible to estimate population means or SDs with our new computer task battery (designed to measure our main outcome, EF’s), and we aimed to include as many schools as was practically possible, a power analysis for this study is not included. Unfortunately, we were not able to reach the recommended critical sample size of 50 at the group level [45]. Statistical techniques to compensate for this potential lack of power for certain multilevel analyses will be considered and investigated carefully. We will assess the effectiveness of the TyM program using multilevel analyses (3 levels: student [n=800], class [n=34], and school [n=13]), to adjust for clustering of observations within a class or school. Randomization took place at the school level. The potential mediation our primary outcome, EF, exerts on our secondary outcomes (healthy behaviors: physical activity and healthy eating) will be investigated using the Baron and Kenny’s method [46], adding EFs as a covariate. Note that the intervention and measurements have been concluded, but the data have not yet been completely analyzed.

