## Methods

### Trial Design

The effectiveness of TyM was investigated in a cluster randomized trial comprising 13 elementary schools, with a total of 34 groups and 800 children. Schools in the control condition continued their regular school curriculum, and would receive the program, or any components thereof, after the third and final measurement (follow-up) had been completed. In this sense, it was a passive control group (though the same amount of time will be spent on similar activities, gym sessions, etc, minus the explicit EF training). All groups of the Dutch sixth and seventh grade of schools in the experimental condition followed the entire TyM intervention for 8 months (25 weeks excluding holidays). This means it is nearly impossible to determine effectiveness per component—our study was set up primarily to answer the question: Can EFs be enhanced through a multi-dimensional training program? If satisfactory results are obtained, TyM can be disentangled in the future to further scrutinize each component separately. Children were to be measured at 3 different time points: preintervention, postintervention, and at follow-up 6 months later. However, the follow-up could not be organized due to financial constraints.

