An effective guide to address socioemotional development while training EFs was found in MindUp [17], in which children learn to recognize and handle emotions in a more functional way [18,19]. The core technique of mindful breathing aids children in finding and maintaining their composure. Pupils learn more about the relationships between thoughts, emotions, and behavior. We adapted the existing MindUp program to our own Dutch target population. All schools already had some kind of socioemotional development program (and allotted weekly time slot), which was replaced by our unified version of MindUp (30 minutes/week for the duration of the trial (25 weeks, excluding holidays), including what we believed were essential components (such as mindful breathing). A teaching manual with additional background information, suggested lesson structures, and hints supported the teachers for these sessions.

The latter 3 modules target EF training, whereas our fourth TyM module aims to change behavior directly; personalized feedback/advice regarding physical activity and healthy eating is generated based on psycho-social determinants that are assessed in the Web-based eHealth module. The feedback is construed through behavior change models such as Reasoned Action Approach [20] and Theory of Planned Behavior [21].

Control groups continued their regular curricula.

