### Secondary Outcomes

As the development of EFs is boosted, we hypothesize various daily life behaviors to benefit from this as well (see secondary hypotheses for an overview of the aspects this study focused on). These outcomes constitute the aforementioned broad transfer and practical relevance of increased EFs; other than stronger EFs, what are the potential benefits for the individual? The case for physical activity and healthy eating is peculiar, as they can not only be affected by increased EFs but also by the tailored feedback eHealth module, which specifically targets these 2 behaviors. 

The eHealth module operates a behavior change model that is almost entirely driven by determinants (of the targeted behaviors), assisted by additional behavior change techniques such as coping plans. These determinants are measured by the program, during the intervention, as personalized feedback is offered to the individual, in response to these determinants and how they evolve over time. However, the very same determinants are also included in the large pre and post-intervention measurements, to allow for comparison with the control group. Measuring these determinants allows us to investigate what changes in determinants drove the change in behavior—useful knowledge in light of similar future behavior change interventions. An overview of the outcome measures is presented in Textbox 1.

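### EF mediation is tested by Baron and Kenny only on activity and eating, which eHealth also targets, so an indirect effect could not credibly be attributed to EF alone

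*Protocol article*

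**What the plan says.** The Statistical Analyses section of the protocol article names the method and the outcomes. On mediation it reads: "The potential mediation our primary outcome, EF, exerts on our secondary outcomes (healthy behaviors: physical activity and healthy eating) will be investigated using". The method named is that of Baron and Kenny, applied by "adding EFs as a covariate". No other outcome is named for mediation.

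The same two behaviours have a second route. The Intervention section says that "our fourth TyM module aims to change behavior directly", in contrast to the three modules that train EF. The Secondary Outcomes section concedes the point for activity and eating: "they can not only be affected by increased EFs but also by the tailored feedback eHealth module, which specifically targets these 2 behaviors".

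Four other statements matter:

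- Secondary Hypotheses lists social, emotional and behavioural problems and school performance beside activity and diet, and then states mediation by EF.
- Trial Design says experimental schools received the whole programme, so that separate component effects can hardly be established. It also says that "the follow-up could not be organized due to financial constraints".
- Secondary Outcomes says the psychosocial determinants of diet and activity are measured before and after the intervention, with comparison to the control group. The mediation sentence does not use them.
- Textbox 1 and the Discussion say CITO scores will be obtained.

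**The concern.** The abstract's second aim is to learn whether increased EF leads to more activity and healthier eating, and this mediation analysis is what would support that statement. Three features weaken it.

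- **The total-effect step.** Baron and Kenny conventionally asks first for a significant arm effect on the outcome. Here that effect can come from eHealth, so passing says nothing about EF. With 13 schools, failing says little either.
- **No estimate.** Adding EF as a covariate and watching the arm coefficient shrink gives neither a size nor an interval for the indirect effect.
- **Attribution.** With the follow-up dropped, EF and behaviour are measured in the same post-intervention round, in children who received every module. Anything that moves both, or behaviour acting on EF, would look like mediation.

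Transfer through EF could therefore be declared when something else linked the two, or missed because the first step failed. School performance, a listed transfer outcome that no module directly targets, has no named mediation test.

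**Working it through.** The plan gives no figure to reproduce: it has no effect size, SD, intraclass correlation (ICC) or alpha, and it states that no power analysis is included. The check is therefore a degrees-of-freedom count plus an illustrative simulation.

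**Inputs from the protocol:** 13 schools, 800 pupils, 3 schools allocated without randomisation (Randomization section).

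**Assumed inputs:** 7 v 6 schools of nearly equal size, school ICC 0.05, residual SD about 1, two-sided 0.05, arm effect on EF (a) about 0.4 SD, direct eHealth effect on behaviour 0 or 0.4 SD, and EF-to-behaviour slope (b) 0 or 0.3. There were 1500 runs per scenario. Arm effects on EF and on behaviour were tested on school means, and b by pupil-level regression with arm in the model. Neither the class level nor pre scores were modelled.

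**Step 1, degrees of freedom for the total effect.** 13 − 2 = 11 with all schools. If the 3 non-randomised schools are set aside, 10 − 2 = 8.

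**Step 2, what drives the total-effect step when EF truly mediates.** The indirect effect is a × b = 0.4 × 0.3 = 0.12 SD in both rows.

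| Direct eHealth effect | Total effect | Total effect significant | All steps pass |
|---|---|---|---|
| 0 | 0.12 | 12% | 10% |
| 0.4 SD | 0.12 + 0.4 = 0.52 | 90% | 65% |

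A closed-form check agrees. With b = 0.3 the behaviour variance components are multiplied by 1 + 0.3² = 1.09. Pupils per school are 800/13 = 61.5. The variance of a school mean is 1.09 × (0.05 + 0.95/61.5) = 0.0713. The SE of the arm difference is √[0.0713 × (1/7 + 1/6)] = 0.149. The critical t on 11 df is 2.20, so an observed difference of about 2.20 × 0.149 = 0.33 SD is needed. True effects of 0.12 and 0.52 give noncentralities of 0.81 and 3.50, and power of about 11% and 89%.

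The EF pathway is identical in the two rows. The pass rate changes because of a path that is not EF.

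**Step 3, false mediation when EF has no effect on behaviour (b = 0) and the direct eHealth effect is 0.4 SD.**

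| Other link between EF and behaviour (assumed) | Mean a × b | All steps pass |
|---|---|---|
| None | 0.00 | 4% |
| Programme engagement drives both (0.3 each) | 0.02 | 13% |
| Unmeasured common cause (0.3 each) | 0.03 | 33% |
| Behaviour feeds back on EF (0.2) | 0.07 | 49% |

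The first row shows that a purely direct effect goes into the remaining arm coefficient (0.40 in that scenario) and leaves the indirect effect unbiased. The other rows show what happens once EF and behaviour are linked for another reason. The documents do not say which row applies, and the design cannot rule out the last three.

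**Step 4, hypothesis against analysis.** Secondary Hypotheses lists four transfer domains above its mediation statement. Statistical Analyses names two. Of the other two, social, emotional and behavioural problems lie close to the socioemotional module, while school performance is targeted by no module.

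**The case against.** A reader might infer that the eHealth module by itself makes the mediation test invalid, or that the test cannot show transfer at all. The documents do not support that. A direct effect is absorbed in the arm coefficient, and the first row of Step 3 confirms it. False mediation needs a further link between EF and behaviour, and the text only leaves that link open. Nor does the text say eHealth changes these behaviours, only that it aims to.

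A reader might also infer that mediation was clearly promised for four outcomes and that school performance was dropped. That is too strong. Aims and Hypotheses ties mediated transfer mainly to activity and eating, as does the abstract's conclusion. The protocol also says school performance will be taken into account in analysis. What stands is a mismatch with the longer list under Secondary Hypotheses and the absence of a named mediation test.

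Other fair points are that the pass rates rest on assumed values, that the simulation uses no pre scores, and that the three-level model may behave differently. The article states neither a total-effect gate nor the absence of an interval, and an analysis plan could add detail. The protocol speaks only of potential mediation, acknowledges the dual path, and says determinant data can show what drove behaviour change. But the method and its outcomes are fixed in the text, and nothing there connects the acknowledgement or the determinants to the EF mediation model.

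Confounding of a non-randomised mediator also affects the method proposed below. That stands, and it is why the conclusion should be worded as associational.

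**Conclusion.** The concern holds as a weakness of method and attribution. It does not touch the primary EF comparison. As planned, the mediation analysis begins with a step that eHealth can satisfy and that 8 to 11 school-level degrees of freedom test weakly, and it ends without an estimate of the indirect effect. Under the stated assumptions, the same indirect effect of 0.12 SD passes all steps in 10% or 65% of runs according to whether eHealth works. With no EF effect at all, the rate is about 4% if nothing else links EF and behaviour, and 13% to 49% under the links tried. These percentages illustrate the mechanism and do not predict this trial's result.

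That EF and behaviour share the post wave, and that all modules go to the same children, does not depend on those assumptions. Mediation therefore cannot credibly be attributed to EF alone.

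**What to change.** - Replace Baron and Kenny by a multilevel product-of-coefficients analysis. Report a × b with a Monte Carlo or school-level bootstrap interval, adjust for pre scores of EF and of the outcome, and drop any total-effect prerequisite.
- For activity and diet, enter the measured determinants (attitude, social influences, self-efficacy) as parallel mediators and report the EF-specific indirect effect. They share the post wave too, so this separates the paths only in part.
- Run the same analysis for school performance (CITO), stating when the test was taken relative to the EF measurement, because the protocol does not say. If the SDQ is added, state that the socioemotional module gives it its own non-EF path.
- Describe total effects on activity and diet as effects of the whole package, and all mediation results as associational.

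The cost is wording and somewhat more modelling on data collected or already planned, together with a more modest conclusion. The lost follow-up cannot be repaired by analysis. The protocol says the data have not yet been completely analysed, so the change can still be made and should be dated.
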